## 2. OBJECTIVES

### 2.1 Primary objective

The primary objective of the proposed pilot study is to gain insight in the effectiveness of a desk-based lighting device with white light containing ultra-low and safe (according to the IEC62471) doses of artificial UVB irradiation in influencing serum 25(OH)D in the Fall/Winter months. Therefore, an ultra-low and safe daily artificial UVB dose is applied during workdays in the home office over a period of eight weeks (eight hours a day) which leads to the primary research question: **To what extent is an ultra-low (<0.5SED, UVI = ~0.06) and safe daily artificial UVB dose, evenly applied during workdays in a home office over a period of eight weeks (eight hours a day) during autumn, able to sustain the summer serum 25(OH)D levels in healthy office workers?**

We hypothesize that the participants exposed to ultra-low doses of UVB during office hours (while working at home in the home office) will demonstrate a less rapid decline in 25(OH)D levels during the eight-week study period than the control group without UVB supplementation.

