### 4.4 Sample size calculation

In order to estimate whether an ultra-low daily dose of artificial UVB (~0.5 SED) complying to the photobiological safety requirements for general lighting could be effective in raising serum 25(OH)D,

simulations based upon Diffey's model were conducted [42]. The simulation results indicate that when the foreseen intervention dose (0.45 SED) is applied in the optimal conditions (evenly over 8 hours and 20 minutes and 10.5 % body surface area exposure), a maintenance of summer serum vitamin D3 levels could be realized. Figure 2 represents the simulation (Exposure: 0.45 SED; Body Surface Area (BSA): 10.5%, front face (3.5%), 2 x back lower arms (3%), 2 x backside hand (3%), neck (1%)) as well as the effect of such an intervention in the foreseen study timespan of eight weeks. For the study it is expected that at optimized conditions a difference of about 17.6 nmol/L between intervention and control group can be realized in those 8 weeks. Having said that, the expected variance in actual exposure each day will be larger based upon the analysis of variations in exposure duration (desk occupancy) and body surface area exposure. The estimated impact of exposure to a minimum 0.225 SED and a body surface area % minimum of 6.5%) on serum vitamin D3 levels are depicted in Table 2.

[figure not shown]

**Figure 2:** Simulations results conducted to estimate the impact of a 8 week UVB exposure of office workers with input parameters (10.5% skin exposure: front face (3.5%), 2 x back lower arms (3%), 2 x backside hand (3%), neck (1%)). At start: 66.4 nmol/L; End intervention group: 61.7 nmol/L (- 4.7 nmol/L); End Control Group: 44.1 nmol/L (-22.3 nmol/L); Expected intervention effectiveness: +17.6 nmol/L. The UVB dose is evenly (UVI=0.06) given over a period of 8 hours and 20 minutes during the workday. This figure is based on exposure during 5 working days.

**Table 2:** Simulation results for expected serum vitamin D3 levels at reduced body surface area (BSA%) exposure and intervention dose (0.225 SED (50%)).

|                             |                                       | Estimated Serum VitD Intervention Effect (nmol/L) compared to control group |                      |                                              |

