## 5. TREATMENT OF SUBJECTS

All home office workers who will participate in the study will be asked to continue their work as they are used to do. During the workday all participants are exposed to the illumination of the existing general indoor lighting in their home. Depending on their desk location, participants may be exposed to daylight entering the office space through windows. This additional light will not contain UVB irradiance as UVB irradiance is absorbed by the window glass.

In addition to the standard lighting the **intervention group** will receive an additional personal desk-based luminaire that is positioned at the side of participant's home desk. The participants in the intervention group will be asked to be seated closer to one side of the desk, where the free floor standing luminaire is positioned, in order to sit more effectively under the luminaire. The area to be seated will be marked on the desk with stickers and tape. Figure 4 demonstrates the desk-based intervention lighting device placed at the side of the desk. Care is taken that the distance between the participant receiving a luminaire and the neighbor (non-participating) colleague/family member is more than 1.6 m to prevent that the (non-participating) colleague/family member is exposed to the ultra-low doses of UVB. The designated workspace of the control group is not altered for the purpose of the study. Control participants will experience only the existing general lighting in their home office).

The desk-based luminaire will emit a continuous ultra-low and safe daily artificial UVB irradiance (actinic UV) of less than 6 mW/m^2 at 20 cm resulting in a received dose by the office worker sitting at his/her desk of about 0.45 SED ((UVI = 0.06) during office hours. The lamps are turned on automatically at 8.50 and off at 17.10 hr. A longer (over)-exposure is therefore not possible. Both groups can do their daily work as they are used to do. Both the participants and the people living in their home will be advised to respect the indicated minimum application distance (80 cm). This minimum application distance keeps the Actinic UV exposure within Risk Group Exempt limits, which allows for a continuous exposure of 30000 sec per day (8 hrs. and 20 minutes) according to the IEC62471 (see form *D6\_2 Photobiological safety IEC 62471 ed 1.0*).

[figure not shown]

**Figure 4.** A picture of a currently designated workspace equipped with the desk-based lighting device.

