## 6.2 Operating behavior

### *First day luminaire behavior*

After the first blood sampling has been taken place, the luminaire will be powered by putting the plug in the mains socket by the technical team. When the luminaire is connected to power it will start with dimmed white light and no UVB. A small amount of white light is emitted to indicate that the luminaire is ON. At noon or when powered after 13.00 hr, the next morning, the luminaire will switch ON (full brightness and UVB) according the preset schedule: ON at 8.50 hr and OFF at 17.10 hr (both the white and UV-B light will turn off). This behavior will also occur in case of a power cycle / disturbance in power.

*Luminaire behavior during the study*

The luminaire will automatically switch ON (full brightness and UVB) at 8.50 hr according to the preset schedule. At 17.10 hr both the white and UV-B light will turn off. This will be repeated for all days during the study period as long as the luminaire is powered. The simultaneous switching on of the visual white light and the UVB lights is an additional visual cue to the participant and other people living in the home to remind them that there is UVB irradiance and that directly looking into the luminaire should be avoided.

The luminaire is equipped with caution labels and a user manual will be supplied to the participant to facilitate proper use of the luminaire and easy access to a contact person if questions pop up.

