Participants will receive the first questionnaire via an e-mail link in the morning of the first assessment day (first blood sampling). The outcome of the first blood sample will be awaited before starting the intervention (installing the luminaire at the desk). This is done so that participants with high vitamin D levels that need medical attention ( $>375$  nmol/L, [41]) can be excluded from the study before receiving any extra UVB exposure (further increasing their vitamin D levels). Although we do not expect such high vitamin D levels, if it occurs, participants will be contacted by the responsible researcher explaining that participating is not possible due to high vitamin D levels in the first blood sampling test. Participants will also be advised to check their level again at their general practitioner to see if a medical reference is needed. In this case, other eligible participants willing to participate will be contacted to ask if they still want to participate. These can replace the participant(s) who drop out.

Installing the luminaire will be conducted by a technical employee from Signify in the homes of the 14 participants in the intervention group. These participants will receive a separate consent form from Signify in which they give written consent that they received the luminaire and that they will not try to sell or open the luminaire, or transfer any information about the luminaire to others during the study period. During the installing process, participants will receive a short explanation about the luminaire (e.g. on and off times, how to switch it off if needed) and they will receive a short manual about the luminaire.

After the installation of the luminaires, the study starts where participants in the intervention group will be exposed to the luminaire between 8:50 and 17:10 during working hours on workdays. In the weekends and between 17:11 and 8:49, the luminaire will be off. This is an automated process. Participants in the control group will not receive the intervention luminaire and only complete the questionnaires and the blood sampling.

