|                                                  | Desk presence | Time outside | Desk presence | Time outside | Desk presence | Time outside | Desk presence | Time outside | Desk presence | Time outside |

|                                                                                  |                       |                       |                       |                       |                       |                       |                       |                       |                       |                       |
|----------------------------------------------------------------------------------|-----------------------|-----------------------|-----------------------|-----------------------|-----------------------|-----------------------|-----------------------|-----------------------|-----------------------|-----------------------|
| 08:50-13:00                                                                      | __ hour(s)
__ min. | __ hour(s)
__ min. | __ hour(s)
__ min. | __ hour(s)
__ min. | __ hour(s)
__ min. | __ hour(s)
__ min. | __ hour(s)
__ min. | __ hour(s)
__ min. | __ hour(s)
__ min. | __ hour(s)
__ min. |
| 13:00-17:10                                                                      | __ hour(s)
__ min. | __ hour(s)
__ min. | __ hour(s)
__ min. | __ hour(s)
__ min. | __ hour(s)
__ min. | __ hour(s)
__ min. | __ hour(s)
__ min. | __ hour(s)
__ min. | __ hour(s)
__ min. | __ hour(s)
__ min. |
| Weekend exposure                                                          |                       |                       |                       |                       |                       |                       |                       |                       |                       |                       |
| Total time outside between 8:50 and 17:10
Saturday                     | __ hour(s)
__ min. |                       |                       |                       |                       |                       |                       |                       |                       |                       |
| Total time outside between 8:50 and 17:10
Sunday                       | __ hour(s)
__ min. |                       |                       |                       |                       |                       |                       |                       |                       |                       |

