## 12.2 Application precautions

The luminaire is calibrated at safe light output values when used as intended (at a distance of >80 cm). Respecting the indicated minimum application distances (up to 80 cm) keeps the Actinic UV exposure within Risk Group Exempt limits, which allows for a continuous exposure of 30000 sec per day (8 hrs and 20 minutes). Being at a closer distance (up to 35 cm) to the luminaire would allow for a continuous exposure of 10000 sec per day (2 hrs. and 45 minutes). At distances closer (looking and staring into the luminaire at close distance) than the indicated 35 cm, a continuous exposure of the luminaire of 1000 sec per day is allowed (15 minutes), but this should be avoided.

Prior to placement the general desk illumination should be measured to check compliancy with local home office illumination. The lighting units are internally set by the manufacturer to come on at 08:50 hr and go off at 17:10 hr when powered, restricting both the lighting and the UV supplementation to these hours of the day, so that a daily dose may not be exceeded. Controls are only accessible to trained personnel. The UV radiation dose will be monitored throughout the trial by trained personnel to ensure that the UV output of the units remains constant (see *D6\_7 Installer manual v2.0*).

As extra precaution, the UV-B irradiance of the lamp will be regularly checked during the study period by the technically trained person (see *D6\_7 Installer manual v2.0*):

- Via solar meter model 6.5 (UV) at 20 cm of the head of the luminaire. UVB irradiance levels on a weekly basis to ensure a consistent dose during the pilot study monitored by a point measurement
- The relative stability will also be monitored through a continuous daily dose measurement is conducted by placing wear shade dosimeters at the desk. The watch is placed a charger.

The desk-based intervention device is labelled with caution labels and a warning not to stare directly into the luminaire. The additional white lighting provides for an additional cue to the users that UVB is irradiated. To ensure proper usage in the application and operating of this engineering sample, participants are asked to adhere to the following guidelines (see *E4 Manual user* and **Figure 5**):

- You do not have to turn on or off the luminaire. This will be conducted automatically.
- Please prevent direct view to the luminaire head
- Please, prevent prolonged exposure to distances shorter than 80 cm.

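### The protocol gives two incompatible weekend schedules for the UVB luminaire, and if the lamp does emit at weekends the diary would miss that exposure

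*Protocol*

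**What the plan says.** **Weekend operation.** Section 7.4 (Study procedures) states: "In the weekends and between 17:11 and 8:49, the luminaire will be off. This is an automated process". Section 6.2 (Operating behavior) describes the switch-on at 8:50 and switch-off at 17:10, with UVB, and adds: "This will be repeated for all days during the study period as long as the luminaire is powered". Section 12.1.2 repeats that sentence. Section 12.2 gives the factory setting without mentioning weekends: "The lighting units are internally set by the manufacturer to come on at 08:50 hr and go off at 17:10 hr when powered". Table 4 in section 12.1.1 also speaks of a daily cycle and is silent on weekends. Switching is not left to the participant: "You do not have to turn on or off the luminaire. This will be conducted automatically" (section 12.2).

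**Intended exposure.** Section 2.1 says that "an ultra-low and safe daily artificial UVB dose is applied during workdays in the home office over a period of eight weeks". The caption to Figure 2 in section 4.4 says "This figure is based on exposure during 5 working days". Section 5 describes the lamp as "resulting in a received dose by the office worker sitting at his/her desk of about 0.45 SED".

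**What is recorded.** In the diary (section 7.4.1.3, Figure 7), desk presence and exposed body areas have columns for Monday to Friday. The Saturday and Sunday rows ask only for "Total time outside between 8:50 and 17:10". Table 3 budgets 40 diary entries, which is 8 weeks of 5 days.

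**What is analysed.** Section 9 compares change in serum 25(OH)D between the groups by ANCOVA, adjusting for average desk presence and time outside. A separate exploratory mixed model uses a UVB dose derived from desk presence and clothing.

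**The concern.** An automatic weekend switch-off and an automatic cycle on every day cannot both be true of the same lamp. All these statements are in the current text, so a reader cannot tell from the protocol on which days the device emits UVB.

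The answer matters because the rest of the design rests on one of the two schedules. The research question concerns a workday dose, the effect size comes from a five-day simulation, and the diary measures a five-day week. The lamp stands in the participant's home, so sitting at the lit desk on a Saturday or Sunday is possible. If the lamp is on then, the participant receives UVB that no diary cell can record. The calculated dose and the desk-presence average would be too low for exactly those participants who use the desk at weekends.

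The timing also matters to household members, who are to stay at least 1.6 m from the lamp (section 12.2) and need to know when it emits.

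**Working it through.** **1. Reproduce the stated daily dose.** Inputs: on-period 08:50 to 17:10 (section 5); 1 SED = 100 J/m² (list of abbreviations); UVI 0.06 (section 5). The protocol does not give the conversion from UVI to irradiance. The usual 25 mW/m² per UVI unit is taken here as an assumption.

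- On-period: 8 h 20 min = 30,000 s.
- Irradiance: 0.06 × 25 = 1.5 mW/m².
- Dose: 0.0015 W/m² × 30,000 s = 45 J/m² = 0.45 SED.

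This matches the protocol's figure. The steps below need only the stated 0.45 SED, not the conversion.

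**2. Ceiling under each schedule,** with full desk presence whenever the lamp is on:

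| Schedule | Lit hours per week | SED per week | SED over 8 weeks |
|---|---|---|---|
| Weekdays only | 5 × 8.33 = 41.7 | 5 × 0.45 = 2.25 | 18.0 |
| All days | 7 × 8.33 = 58.3 | 7 × 0.45 = 3.15 | 25.2 |

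Ratio: 3.15 / 2.25 = 1.4, or +40%. The ceiling per day is 0.45 SED in both rows; only the number of days differs.

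**3. A participant at the 2.5-day minimum** (section 4.2). Weekday dose: 2.5 × 0.45 = 1.125 SED per week. This equals 5 × 0.225, the daily dose behind the planned 8.8 nmol/L difference. The protocol gives no figure for weekend desk time, so a range is assumed:

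| Weekend desk time (full days) | SED per week | Change | Dose the diary would show |
|---|---|---|---|
| 0 | 1.125 | none | 1.125 |
| 0.5 | 1.35 | +20% | 1.125 |
| 1 | 1.575 | +40% | 1.125 |
| 2 | 2.025 | +80% | 1.125 |

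**4. Where the gap would enter.** The exploratory dose model in section 9 takes desk presence and clothing as its inputs, and neither is recorded for weekends. The average desk-presence covariate in the ANCOVA would leave out weekend time for the same reason. The group term in the ANCOVA is allocation, yes or no, and does not use calculated dose.

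**The case against.** **The gap may not exist.** If section 7.4 is right, the Monday to Friday diary covers the whole exposure period and nothing is missing. The objective, the simulation and the 40 diary entries all fit that schedule. This stands: the measurement gap is conditional on weekend emission. The contradiction in the text is not.

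**The schedule can be set.** Section 6.1 says Bluetooth control sets the on-off rhythm, and Table 4 refers to switching times agreed for the test. The conflict may therefore be one of wording and not of hardware. Sections 12.1.1 and 12.2 are merely silent on weekends and are not further contradictions. This also stands. The conflict is between section 7.4 on one side and sections 6.2 and 12.1.2 on the other.

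**Dose is measured another way.** Dosimeters at the desk log daily dose continuously (sections 6.1 and 12.2). They would reveal weekend emission. They would not show whether the participant was there or how much skin was exposed, so the received dose would remain unknown.

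**A stronger reading that does not hold.** A reader might multiply a Table 2 effect by 1.4 to get a serum effect for seven-day use. The documents do not support that. Table 2 varies daily dose, up to 0.45 SED, and body area; it does not vary days per week. It is proportional to daily dose at 10.5% area (17.6 against 8.8 nmol/L) but not to area: 17.6 × 6.5 / 10.5 = 10.9, whereas the table gives 13.6. The factor 1.4 also needs full occupancy on all seven days. A reader might equally infer that the participant information is wrong. It is not at hand, so no mismatch can be asserted.

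**Conclusion.** The protocol is wrong as written: its statements on weekend operation contradict each other and must be reconciled. This review does not say which schedule is right.

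If the lamps emit at weekends, the weekly ceiling is 3.15 instead of 2.25 SED (+40%). For a participant at the 2.5-day minimum, the unrecorded addition would be 20% to 80% for half a day to two full days of weekend desk time. Those figures assume full-day presence at the stated 0.45 SED; real weekend use is not given. The exploratory dose model and the desk-presence covariate would then rest on incomplete exposure data.

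It would go too far to infer that the primary comparison is invalid. It contrasts having the lamp with not having it and does not use calculated dose, so it stands as a device effect. What changes is whether that effect can be described as the effect of a workday dose. The daily ceiling is the same under either schedule. Severity is moderate.

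**What to change.** 1. Reconcile sections 6.2, 7.4, 12.1.2 and 12.2 with the schedule actually programmed, so that all four state the same days and hours. Verify that schedule on each luminaire at installation and record the check.
2. If weekend emission is confirmed, add Saturday and Sunday entries for desk presence and exposed skin to the diary. Use them in both groups, so that the covariate is defined alike. Include them in the calculated UVB dose and in the desk-presence average. Describe the exposure accordingly in the objective and beside the five-day simulation.
3. Check that the participant information and user manual give the same schedule.

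The cost is a few sentences, a schedule check on 14 lamps and, at most, a few extra diary cells per week. It should be done before installation, because weekend desk time that was not recorded cannot be reliably reconstructed afterwards.

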#### **7.4.1 The data assessment weeks**

Week 0, Week 4 and Week 8 are the data assessment weeks, employing the blood sampling and self-report measures (questionnaire via Limesurvey). The participants are also asked to fill in the logbook on a daily basis of which the data is uploaded on Limesurvey weekly (by scan or photo). Participants can also choose to complete the daily diary online right away daily.

##### **7.4.1.1 Blood sampling to measure 25OHD serum levels**

Blood will be sampled three times: in week 0, at pre-scheduled day in week 4, and at pre-scheduled day in week 8 at DVU. The laboratory will analyze the concentration of 25(OH)D in the blood using an immunoassay method. The accuracy of the used analysis method is 95%. Five days after the analysis the remaining blood samples will be destroyed as medical waste. DVU sends anonymous vitamin D values (using a participant ID) to the TU/e researcher who will pseudonymize the data after sending it to the data-analyst.

### 7.4.1.2. Questionnaires

Questionnaires to be found in F1 Questionnaires v2.0 20200515 will be programmed in Limesurvey (a locally installed tool used at the TU/e where only local storage of the data is enabled). The questionnaires are sent via a link to the participants' e-mail on the day of the blood sampling (in the morning). Subsequently, participants can fill in the questionnaires on their own PC/laptop. General levels of fatigue will be measured through the 20 items of the Checklist Individual Strength [43], sleep quality and timing are assessed through 19 items based on the Consensus sleep diary [44] and the Munich Chronotype Questionnaire [45]. The first online questionnaire (sent at day 1 in week 0) also includes questions related to the target group description like age, gender, and vitamin D related food intake (see section 5.1.3; food intake will also be measured in week 4 and 8). Participants will receive a reminder to complete the questionnaire towards the end of the working day if they have not completed the questionnaire yet. They can also do this at home since no IP addresses are saved by the Limesurvey tool.

